## Abstract

**Background:**

Yearly, nearly all the estimated worldwide 2.7 million neonatal deaths occur in low- and middle-income countries. Infections, including those affecting the umbilical cord (omphalitis), are a significant factor in approximately a third of these deaths. In fact, the odds of all-cause mortality are 46% higher among neonates with omphalitis than in those without. Five large randomized controlled trials in Asia and Sub-Saharan Africa (SSA) have examined the effect of multiple cord stump applications with 4% chlorhexidine (CHX) for at least 7 days on the risk of omphalitis and neonatal death. These studies, all community-based, show that multiple CHX applications reduced the risk of omphalitis. Of these trials, only one study from South Asia (the Bangladeshi study) and none from Africa examined the effect of a single application of CHX as soon as possible after birth. In this Bangladeshi trial, CHX led to a reduction in the risk of mild-moderate omphalitis and neonatal death. It is important, in an African setting, to explore the effect of a single application among health-facility births. A single application is programmatically much simpler to implement than daily applications for 7 days. Therefore, our study compares umbilical cord cleansing with a single application of 4% CHX at birth with dry cord care among Ugandan babies born in health facilities, on the risk of omphalitis and severe neonatal illness.

**Methods:**

The CHX study is a facility-based, individually randomized controlled trial that will be conducted among 4760 newborns in Uganda. The primary outcomes are severe illness and omphalitis during the neonatal period. Analysis will be by intention-to-treat.

**Discussion:**

This study will provide novel evidence, from a Sub-Saharan African setting, of the effect of umbilical cord cleansing with a single application of 4% CHX at birth and identify modifiable risk factors for omphalitis.

**Trial registration:**

ClinicalTrials.gov, identifier: NCT02606565. Registered on 12 November 2015.

**Electronic supplementary material:**

The online version of this article (doi:10.1186/s13063-017-2050-0) contains supplementary material, which is available to authorized users.

## Background

Ninety-eight percent of the estimated worldwide 2.7 million annual deaths in the first 28 days of life occur in low- and middle-income countries (LMICs) [1]. Nearly a third of these neonatal deaths are associated with infections and this proportion is higher in areas and countries where nearly half of the births occur at home, such as Uganda [2]. Infection of the umbilical cord stump (omphalitis) is a significant contributor to these infections in newborn babies in LMICs [2, 3]. In a Nepalese study, the odds of all-cause mortality were 46% (95% CI 8–98%) higher among infants with umbilical cord infection than in those without [4]. The umbilical cord is cut after birth and the remaining cord stump generally dries and falls off within 5–15 days [3]. Before it detaches, the stump provides necrotic tissue suitable for bacterial colonization, and can act as an entry point for pathogenic microorganisms into the newborn. Newborns are particularly prone to infection, such as omphalitis, for a number of reasons including an immature immune system, exposure to maternal vaginal organisms during birth and unhygienic practices after birth. These practices include cutting of the cord with unsterile instruments, inadequate hand-washing by birth attendants and other caretakers and topical application of harmful substances such ash and cow dung. The increased risk of infection among newborns is even greater for those born preterm who have a more immature immune system and more vulnerable and thinner skin compared to their term counterparts. Several interventions have been recommended in the past to combat newborn infections [2]. These include: full-body skin cleansing with antiseptics like chlorhexidine (CHX); hand-washing with soap and water and use of clean birth kits. But the effects of these interventions on the incidence of infection and death in neonates have been mixed and two systematic reviews did not unequivocally conclude that any of these interventions reduced the risk of either serious infection or death. The World Health Organization (WHO) recognizes that cord care is a crucial component of immediate newborn care. It currently recommends dry cord care for babies born in health facilities in low-income countries while noting that antiseptics could be used in settings where harmful cord practices are rife [5].

Nonetheless, this WHO recommendation of dry cord care for LMIC facility births is questionable given the inadequate evidence on which it is based. The WHO’s recommendation was based on a Cochrane review by Zupan et al. that found no difference in the incidence of umbilical cord infection when topical antiseptics were compared to placebo. With the exception of one study in Thailand, the rest of the 22 trials included in this review were from high-income countries. It would be problematic to generalize these findings to LMICs. There are several potential topical applications that could be used to lower the risk of neonatal infections and death through appropriate cord care in LMICs, such as CHX, povidone iodine, ethanol, gentian violet, silver sulfadiazine and others. Of these, CHX shows the most promise for the following reasons: (1) low cost, (2) broad-spectrum activity against gram-negative and gram-positive bacteria, (3) strong tissue-binding potential with residual effectiveness and (4) a wide safety record. Several studies have shown that CHX reduces cord stump colonization by bacteria and the WHO recommends it as the preferred agent if an antiseptic is to be used on the cord. In addition, CHX is included in the WHO Essential Drug List and is also identified as one of the commodities in the UN commission’s report on life-saving commodities for women and children.

### State of the existing academic literature on topical application of chlorhexidine to the umbilical cord stump

CHX has been used for decades in various health care settings as an antiseptic and, in most of these cases, it has been shown to reduce bacterial colonization and the risk of infection. With respect to newborn cord care in LMICs, two randomized trials in the 1990s of vaginal and newborn washing with 0.25% CHX showed promise but two more recent studies, one in South Africa using 0.5% and the other in Pakistan using 0.6% CHX, did not find a lower neonatal mortality in the intervention group [2]. A more recent approach has been to apply 4% CHX directly to the umbilical cord stump. We found five published reports of large randomized trials, all community-based, that have been done in LMICs; three in Asia and two in Sub-Saharan Africa (SSA) [6–10]. These studies showed that multiple CHX applications may lead to a marked reduction in the incidence of omphalitis but effects of CHX on neonatal mortality vary considerably (Table 1).

**Table 1 Tab1:** State of the existing academic literature on topical application of chlorhexidine on the umbilical cord stump

		Risk of omphalitis/1000			Neonatal mortality/1000		
Author, Year	Country	Intervention	Control	Adjusted RR	Intervention	Control	Adjusted RR
Mullany, 2006 [6]	Nepal	30.1	62.7	0.46 (0 · 36, 0 · 59)	14.6	19.3	0 · 76 (0 · 55, 1 · 04)
Soofi, 2012 [7]	Pakistan	31.7	75.9	0.58 (0 · 41, 0 · 82)	22.8	36.1	0.62 (0 · 45, 0 · 85)
Arifeen, 2012 [8]	Bangladesh	14.7	26	0.55 (0 · 31, 0 · 95)	26.6	28.3	0.94 (0 · 78, 1 · 14)
Sazawal, 2016 [10]	Tanzania	78.4	115.5	0.65 (0 · 61, 0 · 70)	10.5	11.7	0.90 (0 · 74, 1 · 09)
Semrau, 2016 [9]	Zambia	4.43	6.1	0.73 (0 · 47, 1 · 13)	15.2	13.6	1.12 (0 · 88, 1 · 44)

*RR* risk ratio

With the exception of the Bangladeshi study, all these trials compared at least 7 days of daily CHX application to placebo or dry cord care. The trial in Bangladesh compared a single application of CHX to dry cord care and reported an efficacy of 20% on neonatal mortality (risk ratio 0.80; 95% CI 0.65–0.98) [8]. There was, somewhat surprisingly, no effect of daily cleansing with CHX for 7 days on neonatal mortality.

There is strong evidence for the effect of 7-day CHX application on the risk of omphalitis but the results from the large trial in Bangladesh and the two African trials question whether this translates into a mortality reduction. Daily CHX applications for 1 week have been associated with delayed cord falling which in turn could increase the probability of infection via the cord, and possibly explain the lack of an effect of daily cleansing for 7 days in some studies [11]. A single CHX application could mitigate the reported delay in cord falling when multiple applications are used. There is no data from Africa, and only one study from Asia, that examined the effect of a single application as soon as possible after birth. It is important, in an African setting, to explore the effect of a single application which is also programmatically much simpler to implement than daily application for 7 days. Our study will, therefore, embark on a head-to-head comparison of a single CHX application to dry cord care in birth facilities on omphalitis and severe illness during the neonatal period.

## Study objectives

To measure the effect of newborn cord care with a single cleansing of the umbilical cord stump using 4% CHX on the risk of severe illness among Ugandan neonatesTo measure the effect of umbilical cord cleansing with a single application of 4% CHX at birth on the risk of omphalitis in Ugandan neonates

## Methods/Design

### Study design

This is an individually randomized facility-based controlled trial in which half of the newborns will be randomized to receive the intervention and the other half will receive the standard of care (dry cord care).

### Setting

The trial will be conducted in three health facilities: Mukono Health Center IV, Kawaala Health Center III and Kitebi Health Center III. These three facilities have a monthly combined average of 2400 antenatal visits and 1200 deliveries. Mukono Health Center IV is located within Mukono district while Kitebi and Kawaala Health Centers are located in Kampala district, the capital city of Uganda. Kampala has an estimated resident population of two million while Mukono district, located 25 km from Kampala City has a largely rural population of almost 60,000 people.

### Participants

The study will be carried out among newborns of HIV-1-negative mothers giving birth at the three clinics in Kampala and Mukono districts. Conducting this trial in a homogeneous group of HIV-unexposed (HU) neonates will substantially reduce the risk of imbalance of HIV exposure between study arms and thus mitigate any potential confounding from such an imbalance. Moreover, a finding of CHX protecting babies from severe illness and/or omphalitis among HU neonates can be cautiously generalized to similar populations elsewhere.

### Inclusion criteria

Children born of HIV-1-negative mothers in the three study clinics.

### Exclusion criteria

Newborns with severe congenital anomaliesNewborns with infection of the umbilical cord when bornSeverely ill infants requiring hospitalization immediately after birthChildren of mothers who cannot appropriately give consent within 12 h of birthBabies born with a birth weight of less than 1500 g

### Randomization

For each of the three health centres, a computer-generated random sequence list with permuted blocks of varying size (4, 6 or 8) was generated by CISMAC scientist [name], who is otherwise not involved in the trial. Based on this sequence, children are randomly allocated to intervention or comparison arms in a 1:1 ratio. Concealment is by a cell phone-based application that yields the trial arm allocation only after consent for inclusion has been confirmed.

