### Background characteristics and potential confounders

Using questionnaires and available records, data will be collected on several potential individual-level confounders. These include: maternal age, maternal education, antenatal care attendance, iron supplementation during pregnancy, antibiotic use during the last weeks of pregnancy, premature rupture of membranes, signs of chorioamnionitis, wealth, household size, parity, tetanus vaccination, gestational age, singleton or multiple birth, sex of the infant, birth weight, use of a clean delivery kit, prelacteal feeds, breastfeeding initiation time, infant’s receipt of colostrum, and Bacille Calmette-Guérin (BCG) vaccination. To further describe the population from which our participants are derived and to adjust for any contextual level confounders, we collect data using questionnaires on group/contextual-level factors such as the presence of electricity in the community, and residence (rural versus urban).

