### Sample size

Sample size for primary objective 1: with type 1 error set at 5%, type 2 error at 0.2 (i.e., 80% power), and accounting for 5% attrition, a sample size of 4760 children will be required to detect a 30% relative reduction in the incidence of severe illness following a single cleansing of the umbilical cord stump with the 4% CHX solution. We assumed a 6% risk of severe illness in the control group.

Power calculation for objective 2: setting the type 1 error at 5% and accounting for 5% attrition, a total sample size of 4760 children will yield 96% power to detect a 30% relative reduction in the incidence of omphalitis following a single cleansing of the umbilical cord stump with the 4% CHX solution. The assumed risk of omphalitis in the dry cord care group (comparator) is 11.5% based on recently published data from the trial in Pemba [10].

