### Data analyses

Baseline characteristics of the mothers, their households and the newborns will be compared between the intervention and comparison arms to check for comparability and identify potential confounders. Continuous variables will be summarized using means, medians, standard deviations and interquartile ranges while percentages will be used for categorical variables.

Analysis for both primary objectives will be based on intention-to-treat. Therefore, all infants randomized and enrolled into the study will be included in the final analysis regardless of whether CHX was applied to their umbilical cord stump and surrounding skin or not (Fig. 2: flow chart and Additional file 1: Standard Protocol Items: Recommendations for Interventional Trials (SPIRIT) Checklist). The risks of omphalitis and severe illness in the intervention arm will be compared to those in the comparison arm using binomial regression with a log link to obtain risk ratios (RR). Multivariable analysis will be used to take into account potential confounding. Only confounders whose inclusion in the model results in a substantial (>5%) change in the estimate of the main outcome will be maintained in the final model. Percent protective efficacy will be calculated as (1 − RR) × 100.

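### Randomisation is stratified by health centre, but no centre term is named for the primary analyses and the >5% rule would drop one; the cost is small and conservative

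*Protocol article*

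**What the plan says.** The Randomization section describes one list per centre, "For each of the three health centres, a computer-generated random sequence list with permuted blocks of varying size (4, 6 or 8) was generated", and states that "children are randomly allocated to intervention or comparison arms in a 1:1 ratio". Centre is therefore a stratification factor.

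The Setting section gives a reason to expect different baseline risks: "Mukono Health Center IV is located within Mukono district while Kitebi and Kawaala Health Centers are located in Kampala district", and it describes Mukono's population as mostly rural. It gives no risks or delivery numbers by centre.

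For both primary outcomes, the Data analyses section plans to contrast the two arms "using binomial regression with a log link to obtain risk ratios (RR". Covariate adjustment comes next, governed by one rule: "Only confounders whose inclusion in the model results in a substantial (>5%) change in the estimate of the main outcome will be maintained". No exception is made for the factor used in randomisation.

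The section on background characteristics lists individual covariates and "group/contextual-level factors such as the presence of electricity in the community, and residence (rural versus urban". Health centre is not among them. Residence is at best a partial proxy for it.

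**The concern.** Stratified blocks remove between-centre variation from the comparison of arms. An analysis that ignores centre still counts that variation in its standard error. When centre risks differ, the interval is then a little too wide and the test a little too strict.

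Silence on a centre term could be left to an analysis plan. The difficulty is the selection rule that the article does fix. It tests for confounding, whereas a stratification factor belongs in the model so that the variance matches the design. Because blocking leaves almost no confounding by centre, the rule as written would discard it. At stake are a small loss of power and an analysis that does not follow the randomisation.

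**Working it through.** **Inputs.** From the Sample size section: N = 4,760, 5% attrition, control risks 6% (severe illness) and 11.5% (omphalitis), 30% relative reduction, and "with type 1 error set at 5%, type 2 error at 0.2 (i.e., 80% power), and accounting for 5% attrition". Sidedness is not stated; two-sided is assumed. Analysed: 4,760 × 0.95 = 4,522, or 2,261 per arm. Assumed here: three centres of equal size, and centre risks averaging 6% or 11.5%.

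**Step 1. The plan's own figures.** The pooled two-proportion test at 2,261 per arm gives 78.6% power for 6% v 4.2% (stated 80%) and 97.4% for 11.5% v 8.05% (stated 96%). A Wald test on the log risk ratio, the scale of the planned model, gives 78.1% and 97.3% with no centre differences. That is the baseline for step 3.

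**Step 2. Would the 5% rule keep centre?** With equal arm sizes in every centre, the Mantel-Haenszel risk ratio is Σ(T_k/2) / Σ(C_k/2) = ΣT_k / ΣC_k, where T_k and C_k are the events per arm in centre k. This is the crude ratio, so adjustment changes nothing. With a largest block of 8, the arms in a centre can differ by at most 4 children when a list stops mid-block. For comparison, with assumed risks of 2/6/10%, a 5% shift in a 6% risk is 0.003. Producing it would take 0.003 × 2,261 / (0.10 − 0.02) ≈ 85 children in one arm moved from the lowest-risk to the highest-risk centre.

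Simulation agrees. Four scenarios of 1,000 trials each used blocks of 4, 6 or 8, centre shares of equal thirds or 50/30/20%, and risks of 2/6/10% or 3/11.5/20%. The largest change in the risk ratio was 0.33%, and none exceeded 5%.

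**Step 3. Size of the standard error excess.** With n = 2,261 per arm and mean risk p:

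- SE reported without centre, under the null: √[2(1 − p)/(np)]
- SE actually applying under centre-balanced allocation: √[2 × mean{p_k(1 − p_k)}/(np²)]
- Actual alpha: 2[1 − Φ(1.96 × SE reported/SE actual)]
- Power at RR 0.7: Φ[(|ln 0.7| − 1.96 × SE used)/SE actual], with both SEs recomputed at RR 0.7

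Example, severe illness at 2/6/10%. SE reported = √[1.88/135.66] = 0.1177. Mean p_k² = 0.004667, so mean p_k(1 − p_k) = 0.05533. SE actual = √[0.11067/8.1396] = 0.1166. The ratio is 1.0096 and alpha is 2[1 − Φ(1.979)] = 4.78%.

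| Outcome, assumed centre risks (%) | SE reported | SE actual | Excess | Actual alpha | Power without → with centre |
|---|---|---|---|---|---|
| Severe illness 4/6/8 | 0.1177 | 0.1174 | 0.2% | 4.95% | 78.1 → 78.2% |
| Severe illness 3/6/9 | 0.1177 | 0.1171 | 0.5% | 4.88% | 78.2 → 78.4% |
| Severe illness 2/6/10 | 0.1177 | 0.1166 | 1.0% | 4.78% | 78.2 → 78.7% |
| Severe illness 1/5/12 | 0.1177 | 0.1155 | 1.9% | 4.58% | 78.4 → 79.3% |
| Omphalitis 6/11.5/17 | 0.0825 | 0.0817 | 1.0% | 4.77% | 97.35 → 97.44% |
| Omphalitis 3/11.5/20 | 0.0825 | 0.0805 | 2.5% | 4.46% | 97.48 → 97.70% |

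A deliberately extreme omphalitis spread (2/7.5/25%) gives a 5.1% excess and an alpha of 3.9%.

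**Step 4. Simulation check (20,000 trials per scenario).** For omphalitis at 3/11.5/20% under the null, the log risk ratio had an empirical SD of 0.0806, against a mean reported SE of 0.0826. The unadjusted test rejected in 4.6% of trials and the centre-stratified test in 5.1%. The geometric mean risk ratio was 1.00 under the null and 0.70 under RR 0.7, adjusted or not, so there is no bias.

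**The case against.** The strongest reply is that this is a condensed article, its analysis plan is not shown, and whether a stratification factor enters the model is often settled there. The Data analyses section names a model family and link. It never says that the model is unadjusted, and nothing in it forbids a centre term. The covariate lists are open-ended, so the absence of centre from them is weak evidence. The 5% rule speaks of confounders, and reading it to cover a design factor is an inference.

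Much of this stands. A reader might infer that the protocol commits to a model with arm alone; the text does not say so. What remains is that the only stated route for a covariate into the final model is a rule that centre would fail, with no exemption for it. An analysis plan that kept centre would have to depart from that rule.

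The size is also open to challenge. The document gives no centre risks, so every scenario is assumed. A pattern closer to the Setting section, with two similar urban centres and one different, is milder. At 5/5/8% the between-centre variance is 0.0002 against 0.06 × 0.94 = 0.0564, or about 0.35%, and alpha is about 4.96%. This stands and is why the point is minor.

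Finally, extra terms in a log-binomial model are not free. In sparse subgroups, such as low birth weight or preterm infants, the model may fail to converge or meet empty cells. That stands too, and it limits the fix.

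**Conclusion.** The point holds as a minor one. The design stratifies by centre, no centre term is named for either primary outcome, and the stated selection rule would remove one. Over the assumed risks tabulated (the extreme spread apart), the standard error is about 0.2 to 2.5% too large and actual two-sided alpha about 4.5 to 4.95%. Power falls by about 0.1 to 0.9 points for severe illness and 0.1 to 0.2 points for omphalitis. These figures rest on equal-sized centres, assumed centre risks, a two-sided test, 4,522 analysed, and losses that do not upset the balance within centres. If centre risks are equal, nothing is lost.

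Two stronger conclusions do not follow. A reader might infer that ignoring the stratification makes the inference invalid. It does not: the error is conservative, the risk ratio is unbiased, and type I error is at or below 5%. A reader might also see a centre term as the remedy for severe-illness power that computes at 78.6% against the stated 80%. The gain is under one point, and that gap is a separate sample-size matter.

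**What to change.** In the Data analyses section, state that health centre, as a three-level fixed term, is included in the primary model for both severe illness and omphalitis and is exempt from the 5% rule. Name the fallback if the log-binomial model does not converge: a centre-stratified Mantel-Haenszel risk ratio, or a modified Poisson model with robust standard errors. Include centre in subgroup models only where the data support it.

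The cost is a sentence or two. No new data should be needed, since each centre has its own allocation list and each child's centre should therefore be known. The sample size does not change. The one downside is a small convergence risk, which the fallback covers.

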### Intervention

The intervention is umbilical cord stump cleansing with a single application of 4% CHX solution at birth. The watery solution was obtained from Galentic Pharma in India (http://www.galentic.com) and came in packages of 10-ml dropper bottles. The application is provided by a trained health worker (nurse or midwife) at the health facility as soon as possible and no later than 12 h after birth. The solution is applied using the dropper bottle onto the tip of the infant’s umbilical cord stump, its base and the area of skin surrounding it. A CHX-moistened cotton ball is then used to gently cleanse the base of the stump and the surrounding skin. Health workers have been trained by general physicians and pediatricians to correctly, consistently and safely apply CHX. Five CHX containers will be randomly chosen early, during and towards the end of the trial to check for CHX concentration and antibacterial activity. The chlorhexidine stock is securely kept below 30 °C, away from light in tightly closed/sealed bottles.

